### 2.11. Statistical Analysis

All statistical analyses will be conducted using IBM SPSS Statistics, version 30.0.0, and R, version 4.5.0. The threshold for statistical significance will be set at α = 0.05. Two-tailed tests will be used unless a specific directional hypothesis is stated (e.g., the anticipated superiority of ETV over VPS), in which case one-tailed tests will be applied.

Continuous variables will first be tested for normality using the Kolmogorov–Smirnov test, and for homogeneity of variance using Levene’s test. If assumptions of normality and homoscedasticity are met, parametric tests such as the independent-samples *t*-test will be used. For repeated measures data, linear mixed-effects models will be applied instead of a traditional ANOVA to account for intra-subject variability and missing data points. If assumptions are violated, appropriate non-parametric alternatives (e.g., Mann–Whitney U test, Wilcoxon signed-rank test) will be applied.

To control Type I errors in multiple comparisons, a Bonferroni correction will be applied where appropriate. In addition to *p*-values, effect sizes (e.g., Cohen’s d for *t*-tests, η^2^ or partial η^2^ for ANOVA) will be reported to quantify the magnitude of observed effects.

For the analysis of longitudinal data, mixed-effects models will be used to account for intra-subject variability across follow-up points. These models will include fixed effects for time and the treatment group, as well as random intercepts to capture individual-level variability.

An a priori power analysis was performed assuming an effect size of Cohen’s d = 0.5, power (1 − β) of 0.80, and α = 0.05 (two-tailed). The estimated required sample size was 51 participants per group. This effect size was selected as a conservative estimate based on previously published studies evaluating pre- and postoperative cognitive and motor changes in patients with iNPH. Nonetheless, we recognize that this estimate may be optimistic. If the true effect is smaller, a larger sample size would be needed to retain adequate statistical power. This limitation is acknowledged, and future extensions of the study may involve adaptive or sequential design strategies to account for observed variability.

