
### Primary and Secondary Endpoints

This study’s primary outcome is the quantification of improvement in cognitive and motor performance from baseline to 12 months after VPS surgery or ETV. Secondary outcomes include the rate of postoperative complications (e.g., infection, device malfunction, or over-drainage), length of hospitalization, ICU stay, and patient-reported quality of life. To ensure that the study has sufficient power to detect meaningful differences between the two surgical groups, a power analysis was conducted. This analysis determined that a total sample size of 100 patients (50 in each group) would be required to achieve a power of 80% to detect an effect size (d) of 0.5 at a significance level of 0.05. The randomized controlled trial design, combined with standardized surgical protocols and the use of advanced neuroimaging and neurostimulation techniques, ensures that the results will be both statistically robust and clinically relevant.

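### The article gives two conflicting rules for the longitudinal outcomes: an unconditional mixed model, and a pre-test-driven fallback to rank tests, one of which cannot compare ETV with VPS

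*Protocol article*

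**What the plan says.** Four statements in section 2.11 (Statistical Analysis) of the protocol article bear on this, in this order:

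1. The pre-tests: "Continuous variables will first be tested for normality using the Kolmogorov–Smirnov test, and for homogeneity of variance using Levene’s test".
2. What follows if they pass: "If assumptions of normality and homoscedasticity are met, parametric tests such as the independent-samples" t-test. For repeated measures, "linear mixed-effects models will be applied instead of a traditional ANOVA to account for intra-subject variability and missing data points".
3. What follows if they fail, in the next sentence: "If assumptions are violated, appropriate non-parametric alternatives (e.g., Mann–Whitney U test, Wilcoxon signed-rank test) will be applied".
4. Two paragraphs later, for longitudinal data: "mixed-effects models will be used to account for intra-subject variability across follow-up points". No condition is attached. The terms are then listed: "These models will include fixed effects for time and the treatment group, as well as random intercepts".

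The section Primary and Secondary Endpoints defines the primary outcome as "the quantification of improvement in cognitive and motor performance from baseline to 12 months after VPS surgery or ETV". Section 2.10 sets visits at 1 week and 3, 6 and 12 months. The primary outcome is therefore a repeated measure, to be compared between two randomised arms of 50.

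**The concern.** Statements 3 and 4 cannot both govern a repeated outcome whose distribution fails the pre-test. One sends it to a rank test and the other keeps it in the mixed model. Timed motor tests are usually right-skewed, so TUG, a named motor outcome, is a likely case.

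Three things are at stake.

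- **Choice after the data.** An analyst with a skewed outcome could cite the article for either method, with both results in view.
- **Wrong question.** The signed-rank test compares paired values in the same patients. It says whether an arm changed, not whether ETV differs from VPS.
- **Lost information.** A Mann–Whitney test at one visit ignores the other visits and every patient without a value at that visit. Within-patient correlation and missing data are the article's own reasons for choosing mixed models.

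The gate also examines the wrong quantity. It tests the variables, whereas a linear mixed model's assumptions concern its residuals and random effects.

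**Working it through.** **Step 1. Does the fallback reach repeated outcomes?**

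| Reading | Text in favour |
|---|---|
| Yes | The fallback sentence directly follows the mixed-model sentence. It refers to assumptions in general, has no restriction to single-visit variables, and names a paired test, which needs at least two values per patient. |
| No | The later sentence gives longitudinal data to mixed models without condition and lists the model terms. |

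Both readings have textual support and no sentence ranks one above the other. The text leaves the method open.

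**Step 2. How often would the gate fire?** The article gives no distribution for any outcome, so these inputs are assumptions: one log-normal variable, N = 100 (the planned total), test level 0.05. Simulated rejection rates:

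| Log-SD | Lilliefors-corrected | Uncorrected, mean and SD estimated from the data |
|---|---|---|
| 0.3 | about 60% | about 5% |
| 0.4 | about 82% | about 18% |
| 0.5 | about 95% | about 42% |

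In a second set-up, Kolmogorov–Smirnov was applied in each arm of 50 together with Levene's test, and the gate counted as fired if any test rejected. On truly normal data it fired in 13% of trials with the correction and 5% without. At log-SD 0.5 the figures were 92% and 29%. The article names "Continuous variables will first be tested for normality using the Kolmogorov–Smirnov test" without saying which version is meant. The same data could therefore go to different analyses on an unstated option.

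**Step 3. What does the signed-rank test answer?** Assume the same true improvement in both arms, so no treatment difference, with 50 patients per arm.

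- With improvement equal to 0.5 SD of the change score, the signed-rank test rejects within a given arm in 93% of trials. The chance that one arm is significant and the other is not is 2 × p × (1 − p) = 2 × 0.93 × 0.07 = 0.13. The simulation gave 14%.
- With improvement equal to 0.5 SD of the outcome and an assumed pre–post correlation of 0.6, the SD of change is √(2 × (1 − 0.6)) = 0.894, so the standardised change is 0.5 / 0.894 = 0.56. Discordant results then occur in about 7% of trials.
- Mann–Whitney between arms, in the first scenario, rejects in 4%, as it should under no difference.

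A high within-arm rejection rate with no arm difference shows that the test carries no information on ETV versus VPS. The article itself expects gait to improve in both arms (section 3, Expected Results).

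**Step 4. What does a single-visit Mann–Whitney test leave out?** It uses one of four postoperative visits. Patients without that visit drop out of the test. At an assumed 15% missing at 12 months, that is 0.15 × 100 = 15 patients, whose earlier visits the mixed model would still use.

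**The case against.** The strongest reply is that section 2.11 can be read coherently. The pre-tests choose between t-test and Mann–Whitney for single-time variables such as hospital or ICU stay, and repeated outcomes go to the mixed model, as the later sentence says. On that reading the primary analysis never changes. This reading is available, and it rules out saying that the fallback definitely replaces the primary model. It does not remove the problem, because the fallback sentence carries no such limit and a paired test has no place among single-time comparisons.

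A second reply is that the signed-rank test is only an example under the word appropriate, and nothing says it will decide ETV versus VPS. That is fair. It could serve to describe change within an arm, and the fault is that the article does not confine it to that use.

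A third is that transformations, residual checks and robust errors belong in the SAP, which is not shown. That also stands: their absence is not the point. The point is the two rules that the article does state.

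A reader might also infer three stronger things that the documents do not support:

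- **That the fallback discards baseline.** Signed-rank on pre–post pairs uses it, and so does Mann–Whitney on change scores. The mixed model as described states no baseline covariate, so no stated adjustment is lost.
- **That the gate costs a large amount of power.** A contrast of 68% for Mann–Whitney on 12-month values with 81% to 93% for a log-scale, baseline-adjusted model (assumed correlation 0.5 to 0.7) reflects mostly baseline adjustment, a separate matter. Like for like at 12 months, with log-SD 0.4 and 50 per arm, Mann–Whitney has 67–68%, a raw t-test 66–68% and a log-scale t-test 70–71%. The rank test costs roughly 0 to 4 points.
- **That some outcome is quite likely to be switched by chance.** A figure of 1 − 0.95^10 = 40% needs ten independent normal variables. Instruments measured on the same patients are correlated.

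**Conclusion.** The point holds as a conflict in the stated plan. Section 2.11 gives an unconditional mixed model and a conditional rank-test fallback for the same longitudinal outcomes, and does not say which prevails. For a skewed outcome such as TUG the method can therefore be settled after the data are seen.

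The size is best expressed as how often the question would arise: about 82% or about 18% of trials at log-SD 0.4 and N = 100, depending on the unstated Kolmogorov–Smirnov version. The log-normal shape and log-SD are assumptions. That the signed-rank test cannot compare independent arms, and that a single-visit test forgoes the other visits and the model's missing-data handling, follow from the tests themselves and need no assumption.

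A reader might conclude that the primary analysis will change with a preliminary p-value. The documents support only that it could. The issue should be resolved before analysis, but it does not undermine the design.

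**What to change.** Amend section 2.11 and carry the same wording into the SAP:

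- Remove the Kolmogorov–Smirnov and Levene gate for repeated outcomes.
- State that the between-arm mixed model is the analysis of every continuous repeated outcome, whatever any pre-test shows.
- Check assumptions on the model residuals.
- Pre-specify how skewness is handled: a transformation (for example log for timed tests) or robust or bootstrap inference.
- Keep Mann–Whitney for skewed single-time outcomes such as length of stay, and as a sensitivity analysis for repeated ones.
- Limit signed-rank tests to within-arm description, with no treatment conclusion drawn from them.

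The cost is protocol and SAP wording only. Sample size, visits and data collection do not change.

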The methodological approach of this study is designed to overcome many of the limitations observed in previous research. By using a randomized controlled design with a sufficiently powered sample size of 100 patients (50 in the ETV group and 50 in the VPS group), this study will provide a statistically robust comparison of the two surgical techniques. The a priori power analysis assumed a medium effect size (Cohen’s d = 0.5), α = 0.05, and power of 80%. While this provides a practical sample estimate, we acknowledge that the true effect size may be smaller than anticipated, potentially requiring a larger cohort to maintain adequate statistical power. This limitation is recognized in the design and discussed transparently.

To ensure procedural consistency across participating institutions, all surgical teams will follow a shared and standardized operative protocol, developed collaboratively by the study investigators. Pre-trial workshops and training sessions will be organized to align technical approaches and perioperative care pathways. In addition, a central monitoring committee will oversee compliance with the protocol and conduct periodic audits to mitigate variability and ensure methodological integrity throughout the multicenter implementation.

In terms of radiological criteria, the diagnosis of iNPH and anatomical suitability for surgical procedures will also be based on the validated indices. In particular, the Evans index—defined as the ratio between the maximum width of the frontal horns and the inner diameter of the skull—will be used to confirm ventriculomegaly when greater than 0.3. Likewise, the callosal angle, measured in the coronal plane through the posterior commissure, provides additional diagnostic confidence, with angles below 90° typically associated with iNPH.

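### Bonferroni is valid, but Holm's step-down procedure gives the same family-wise error control, is never less powerful, and costs one phrase to adopt

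*Protocol article*

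**What the plan says.** Section 2.11 of the protocol article gives one sentence on multiplicity. It says that, to limit false positive findings across several comparisons, "a Bonferroni correction will be applied where appropriate". It names no other procedure, does not say which comparisons form the family or how many there are, and does not say whether the correction is single-step. The plain reading is that each of k tests is held to alpha/k.

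The same section sets the overall level ("The threshold for statistical significance will be set at α = 0.05"). It makes tests two-tailed by default, with an exception for directional hypotheses ("in which case one-tailed tests will be applied").

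The section on primary and secondary endpoints defines the primary outcome as "the quantification of improvement in cognitive and motor performance from baseline to 12 months", so it covers two domains. Sections 2.2 and 2.3 list several instruments for them. The sample size rests on "a medium effect size (Cohen’s d = 0.5), α = 0.05, and power of 80" per cent (section 4), with no adjustment of alpha for multiple tests.

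**The concern.** When a family holds two or more tests, single-step Bonferroni keeps every test at alpha/k whatever the other tests show. Holm orders the p-values and compares the smallest with alpha/k, the next with alpha/(k − 1), and so on until one fails. Both procedures hold the family-wise error at or below alpha with no assumption about dependence. For hypothesis testing, Holm is therefore never worse.

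With one cognitive and one motor test, once either passes at 0.025 Holm tests the other at 0.05, while Bonferroni still demands 0.025. At stake is a real difference in a second domain that is missed more often than the error control requires. That matters more than usual here, because the trial compares the procedures on both cognition and movement and has little power to spare.

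**Working it through.** **Inputs from the protocol article.** d = 0.5, alpha = 0.05 two-tailed, "power (1 − β) of 0.80" (section 2.11); 50 per arm (endpoints section). Section 2.11 gives 51 per group as the requirement.

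**Assumptions, not in the document.** Number of tests k, true effect in each test, and correlation ρ between test statistics.

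**1. The plan's own sample size.** n per arm = 2(z₁ + z₂)²/d².
- Two-sided: 2(1.960 + 0.842)²/0.25 = 62.8, so 63 (64 by the exact t-test).
- One-sided: 2(1.645 + 0.842)²/0.25 = 49.5, so 50 (51 by the exact t-test).

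The stated 51 is reproduced only by a one-sided test. With 50 per arm and two-sided 0.05, power is 0.705 (0.697 by the t-test). This is background only; it does not arise from the choice of multiplicity procedure.

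**2. Power of a single test at each level.** Noncentrality = 0.5 × √(50/2) = 2.5.
- At two-sided 0.05: 0.705.
- At two-sided 0.025: 0.602 (0.590 by the t-test).
- Difference: 0.705 − 0.602 = 0.103.

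**3. Two tests, both effects real, ρ = 0.**
- At least one rejection, either method: 1 − (1 − 0.602)² = 0.842.
- Per-test power, Bonferroni: 0.602. Holm: 0.602 + 0.103 × 0.602 = 0.664.
- Both rejected, Bonferroni: 0.602² = 0.362. Holm: 0.705² − 0.103² = 0.486.

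**4. Two tests, both effects real, correlated.** Simulation of 400,000 pairs of normal test statistics:

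| ρ | At least one (either method) | Per test, Bonferroni | Per test, Holm | Both, Bonferroni | Both, Holm |
|---|---|---|---|---|---|
| 0 | 0.843 | 0.603 | 0.665 | 0.363 | 0.487 |
| 0.3 | 0.796 | 0.602 | 0.660 | 0.408 | 0.523 |
| 0.5 | 0.761 | 0.600 | 0.655 | 0.439 | 0.549 |

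The row for ρ = 0 agrees with the hand calculation to within simulation error and rounding.

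**5. Two tests, only one effect real.** Holm helps only if the null test is itself rejected at 0.025. For ρ = 0 the gain is 0.103 × 0.025 = 0.003, or 0.3 percentage points. In the simulation, power for the real effect was 0.602–0.603 under Bonferroni and 0.604–0.605 under Holm (ρ from 0 to 0.5).

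**6. Larger families, all effects d = 0.5.** Average power per test, Bonferroni against Holm:
- 4 tests: 50% against 59%.
- 5 tests: 47% against 56%.
- 6 tests: about 45% against 54%.
- 10 tests: 38% against 45–47%.

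**7. Error control.** With both of two hypotheses null, the simulated family-wise error was the same under either method, 0.046 to 0.050 for ρ from 0 to 0.5. With one null it was about 0.025 for Bonferroni and 0.039 to 0.040 for Holm. Holm uses error allowance that Bonferroni leaves unspent and stays below 0.05.

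**The case against.** The strongest reply is that nothing here is wrong. Bonferroni is a valid procedure, nothing else in the article contradicts it, and a condensed article may leave the exact variant and the family to an analysis plan that is not shown. That stands, and it is why the point is an improvement and not an error.

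A reader might infer that the plan's correction always costs power across the cognitive and motor domains. The document does not support that. It never says that the correction runs across the two domains; the comparisons meant could equally be follow-up times or instruments. The gain also depends on more than one effect being real. Section 3 expects gait to improve in both arms and says that cognitive improvement may differ between them. If cognition alone truly differs, step 5 applies and the gain is negligible.

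The reply also notes that Bonferroni gives simple simultaneous confidence intervals, and that the article wants to speak of comparable, superior or non-inferior results, which are often judged from intervals. This is a real cost of switching. It is a modest one, because section 2.11 promises p-values and effect sizes and does not mention simultaneous intervals.

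What survives the reply is the dominance itself. For testing, Holm needs no extra assumption and is never less powerful, and the article gives no reason for preferring the weaker procedure.

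**Conclusion.** The point holds as a cheap improvement of low severity. If both of two effects are real at d = 0.5, with 50 per arm, two-sided testing and correlation 0 to 0.5, Holm adds about 6 percentage points of average power per test and 11 to 12 points to the chance of showing both. It adds nothing to the chance of at least one rejection, and almost nothing when only one effect is real. The family size, effects and correlations are assumptions, so the size of the gain in this trial cannot be read from the document.

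Two stronger readings should be resisted. The plan's error control is not defective. Nor would the change cure the trial's lack of power: that comes from a sample size that fits a one-sided calculation and an unadjusted alpha, and even under Holm average power per test at two primary tests stays near 66%, well below 80%.

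**What to change.** In section 2.11, replace *a Bonferroni correction* with *the Holm step-down (Holm–Bonferroni) procedure at family-wise alpha 0.05*. Apply it to whichever family of comparisons the sponsor was going to correct, and report Holm-adjusted p-values. Holm ranks p-values within a family, so that family has to be fixed before the data are seen, in the analysis plan if not in the article. The change neither settles nor alters the rule on one-tailed tests.

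The cost is one phrase, with no new data and no extra patients. Simultaneous confidence intervals that match Holm are less simple than Bonferroni's. Intervals shown beside the adjusted p-values should therefore be labelled as unadjusted, with a note that they can disagree with the adjusted result. Alternatively, Bonferroni intervals can be kept for any claim that rests on an interval. The sample-size shortfall needs its own correction.
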